### Primary statistical plan and sample size considerations

The sample size was calculated in order to determine a 15% difference in the diagnostic yield between the individual modalities and their combined use owing to the expected better and synergistic diagnostic yield. The estimated difference in the diagnostic yield (67% vs. 82%) is based on previously conducted large-scaled observational studies and meta-analyses that suggested an improved diagnostic yield with the use of needle aspiration and a combination of both modalities [11, 12, 14, 16]. The calculation was based on this difference in the diagnostic accuracy for equality of paired proportions with a two-sided significance level of 0.05 and 80% power. Assuming that the response with needle biopsy is independent of the response with forceps biopsy, the percentage of participants with discordant results for the two modalities was estimated to be 39%. With an estimated dropout rate of 5% due to the loss of patients during follow-up, we estimated a sample size of 142 participants (71 in each group, and 142 biopsies for each modality and combination). The sample size was calculated using PASS 2021 (NCSS, LLC., Kaysville, UT, USA).

Baseline demographic, clinical, and radiological characteristics of the participants as well as the procedural details and outcomes will be presented as means with standard deviation (SD) for continuous data and frequencies with proportions for categorical data. Characteristics will be analyzed using the *t*-test (or Wilcoxon’s rank-sum test) for continuous variables and the chi-square test (or Fisher’s exact test) for categorical variables. Since each patient will have two results from separate modalities, it should be considered that two outcomes from the same patient are likely to be more similar than two results from different patients. To compare the paired proportions, McNemar’s test will be used. A *p*-value < 0.05 indicates statistical significance. All analyses will be performed using STATA version 16.0 (StataCorp., College Station, TX, USA). A preliminary analysis is prespecified when all the enrolled participants undergo ENB with available initial pathological reports and 1-month follow-up.

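### The 39% discordance does not fit the single-tool versus combined comparison that the sample size names, so the stated 80% power is not the power of that comparison; the trial is oversized for it, not underpowered

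*Protocol article*

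**What the plan says.** Under *Primary statistical plan and sample size considerations*, the protocol article says the sample size was chosen "to determine a 15% difference in the diagnostic yield between the individual modalities and their combined use". The yields given are 67% and 82%. The calculation is for "equality of paired proportions with a two-sided significance level of 0.05 and 80% power".

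The discordance is derived by taking needle and forceps results as independent of each other. On that basis the article reports that "the percentage of participants with discordant results for the two modalities was estimated to be 39" per cent. After an allowance of 5% for loss to follow-up, the total becomes 142, with every participant contributing a needle result, a forceps result and a combined result. McNemar's test is the planned test for paired proportions.

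Two other places bear on what the combined result is. *Diagnosis and follow-up* calls a case positive for malignancy if any of the needle, forceps or lavage samples is positive. Table 2, under *Objectives and endpoints*, evaluates needle, forceps and their combination separately.

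**The concern.** The power of McNemar's test depends on the difference and on the proportion of discordant pairs. The pair named here is one tool against both tools in the same patient. A lesion diagnosed by the needle is then also diagnosed by the needle plus forceps, so one of the two discordant cells is empty and the discordant proportion can only be the gain itself. A 39% discordance with a 15-point gain would need 12% of participants to be diagnosed by the single tool but not by the combination: (39 − 15)/2 = 12.

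This derivation is the article's only justification for 142 participants having an invasive procedure. If its discordance belongs to another comparison, the stated 80% does not describe the comparison that a reader will attach it to. It also hides that a significant McNemar result for combined versus single is nearly assured at this size, so the informative result is the size of the gain.

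**Working it through.** **Inputs.** From the sample size section: yields 67% and 82%, so d = 0.15; two-sided alpha 0.05 (z = 1.960); power 80% (z = 0.8416); discordance pd = 0.39; dropout 5%; total 142.

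**Formula (McNemar, normal approximation).** n = [1.960·√pd + 0.8416·√(pd − d²)]² / d².

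**1. The plan's own figure.** With pd = 0.39:
- 1.960·√0.39 = 1.2240, and 0.8416·√(0.39 − 0.0225) = 0.5102.
- n = (1.7342)²/0.0225 = 133.7, rounded up to 134.
- 134/0.95 = 141.05, rounded up to 142.

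The 142 is reproduced, so the arithmetic after the 39% is sound.

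**2. Where 39% can come from.** Two independent results with yields 67% and 82% give 0.67 × 0.18 + 0.33 × 0.82 = 0.1206 + 0.2706 = 39.1%.

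**3. Other readings, keeping needle and forceps independent.**

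| Reading | Needle–forceps discordance | Combined yield |
|---|---|---|
| Both tools 67% | 2 × 0.67 × 0.33 = 44.2% | 1 − 0.33² = 89.1% |
| One tool 67%, combination fixed at 82% | other tool 0.15/0.33 = 45.5%; discordance 51.5% | 82% |
| Tools 67% and 82% | 39.1% | 1 − 0.33 × 0.18 = 94.1% |

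Only the last row gives 39%. It makes 82% the yield of one tool, which is not how the article defines it.

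**4. The named comparison, with the combined result containing the single one.** Here pd = d = 0.15, all in one direction:
- 1.960·√0.15 = 0.7591, and 0.8416·√(0.15 − 0.0225) = 0.3005.
- n = (1.0596)²/0.0225 = 49.9, rounded up to 50.
- 50/0.95 = 52.6, rounded up to 53.

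The exact McNemar test needs 52 evaluable.

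**5. Power at the planned size.** 142 × 0.95 = 134.9, about 135 evaluable.
- Normal approximation: Φ[(0.15·√135 − 0.7591)/√0.1275] = Φ(0.9838/0.3571) = 99.7%.
- Exact test: with all discordant pairs one way, significance needs at least 6 of them, and P(Bin(135, 0.15) ≥ 6) is above 99.9%.
- A gain of only 6 points already has about 83% exact power.

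**6. Precision of the gain.** At 135 evaluable and a 15% gain, the exact 95% interval is about 9% to 22%.

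**7. Needle versus forceps, as an assumption only.** The article gives no separate tool yields. Suppose the combined yield is 82%. The difference detectable with 80% power at 135 evaluable (same formula) is then:
- 67% is the lower of the two tools: pd = 0.30 − d, about 10.5 points.
- The two tools average 67%: pd = 0.30, about 13 points.
- 67% is the higher of the two tools: pd = 0.30 + d, about 16 points.

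**The case against.** The strongest reply is that the article never says the combined result was treated as an independent test. It states independence between needle and forceps, and 39% is correct for that pair if 67% and 82% are the two tools' own yields. This part stands: the match in step 2 shows which margins fit, not how the calculation was set up, and a reader should not take the mechanism as established. It does not rescue the 80%, because on that reading the power belongs to needle versus forceps while the article attaches it to single versus combined.

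Second, the error is harmless in direction. This also stands. The trial is larger than the named comparison needs, and neither the endpoint, the test nor the number of participants has to change. A reader who sees a wrong discordance might infer that the trial is underpowered; for the named comparison the opposite is true.

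Third, a reader might infer that the article contradicts itself, since it assumes independence and later remarks that "two outcomes from the same patient are likely to be more similar than two results from different patients". That inference is not supported. The remark motivates a paired analysis. Independence is a planning value and, if within-patient correlation is not negative, it gives the largest discordance for given tool yields and so the largest sample size.

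Fourth, a reader might go on to say that needle versus forceps has too little power. Without separate yields the documents cannot settle that, and step 7 is only a range under stated assumptions.

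**Conclusion.** The point holds in this form: 39% is not the discordance of the comparison for which the trial is sized, and on any reading 80% is not that comparison's power. For 67% versus 82% with an either-tool combination, discordance is 15%. The required number is 50 evaluable (53 with dropout) rather than 134 (142), and power at 135 evaluable is at least 99.7%.

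This rests on the combination counting as diagnostic when either tool does. That is explicit for malignancy in *Diagnosis and follow-up* and is inferred for benign diagnoses. Counting lavage cytology as well can only add diagnoses, so it does not break the containment. The fault lies in the justification of the sample size. It does not threaten the trial's ability to answer the named question.

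**What to change.** Keep 142 and rewrite the derivation:

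- State which comparison the figures 67%, 82% and 39% describe.
- For single tool versus combination, say that the combined result contains the single-tool result, replace 39% by a one-way discordance of 15%, remove the independence assumption from that derivation, and restate the power as above 99% at about 135 evaluable.
- Present the gain with its confidence interval as the main result of that comparison (15%, 95% CI about 9% to 22% as the planning value), because significance alone will say little.
- If needle versus forceps is mentioned, label the tool yields as assumptions and give a range (about 10.5 to 16 points detectable with 80% power), not a single figure.

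The cost is one rewritten paragraph. No participants, procedures or tests change. Enrolment was under way when the article was written, so the change should be presented as a corrected justification of a number already fixed.

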### Diagnosis and follow-up

All cases with histopathologically confirmed malignancy based on either ENB-guided needle biopsy or cytology, forceps biopsy, or BAL cytology are determined as positive for malignancy. The histopathological results of the biopsied samples that reveal no malignancy or indeterminate findings are initially considered negative. In such cases, the attending physician will conduct follow-up for at least 12 months and make decisions to perform additional invasive procedures to determine the true diagnosis (gold standard) accordingly. The final diagnosis will be determined at 12 months from the procedure. The following cases will be defined as false negatives: (1) malignancy based on a repeat biopsy (e.g., surgical biopsy, CT-guided TTNA, and bronchoscopic); (2) growth of the lesion observed on serial follow-up CT within 12 months; (3) treated as lung cancer without pathological confirmation; and (4) lung cancer diagnosed at other sites (including non-index lesions or lymph nodes diagnosed using linear EBUS during or after the index procedure) within 6 months. The following cases will be defined as true negatives: (1) subsequent diagnostic procedures confirm a non-malignant diagnosis; (2) an initial non-malignant lesion resolved without cancer treatment (e.g., improved proven infectious disease or transient inflammation); or (3) no lesion progression observed on radiographic follow-up for 12 months.

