### Objectives and endpoints

The primary endpoint is the diagnostic performance of ENB-guided needle biopsy and forceps biopsy and the yield achieved by combining the modalities based on the 12-month clinical follow-up. Secondary endpoints include a comparison of successful approach to the lesion, duration of sampling time, number of attempts, and successful acquisition of core tissue between the needle and forceps biopsy techniques. Additionally, all adverse events related to the ENB procedure or sedatives will be captured and classified according to the Common Terminology Criteria for Adverse Events (CTCAE) scale, version 5.0 [26]. Pneumothorax will be confirmed using chest X-rays performed post-procedurally and the day after the procedure. All participants will be followed up at 2 weeks post-procedure to evaluate the presence of delayed complications. The detailed definitions of outcomes are presented in Table 2.

**Table 2 Tab2:** Definitions and overview of study endpoints

Primary endpoint: diagnostic values
- Primary endpoints will be calculated separately for needle aspiration, forceps biopsy, and the combination of the two. For initially negative results, the final diagnosis will be confirmed based on the 12 months of clinical follow-up
- Diagnostic accuracy:
Proportion of subjects in whom the ENB-guided biopsy yielded a definite diagnosis = (malignant and benign diagnosis by modality)/(biopsied lung lesions)
- Sensitivity:
= (Malignancy confirmed by modality)/(Number of malignancies confirmed at 12-month follow-up)
- Specificity:
= (Benign confirmed by modality)/(Number of benign lesions confirmed at 12-month follow-up)
- Positive predictive value:
= (True malignant lesions)/(Number of malignant lesions by modality)
- Negative predictive value:
= (True benign lesions)/(Number of benign lesions by modality)

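### Sensitivity drops any missed cancer that is lost to follow-up, because only index-negative patients can lack a final diagnosis

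*Protocol article*

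**What the plan says.** Under Diagnosis and follow-up, malignancy found on needle biopsy or cytology, "forceps biopsy, or BAL cytology are determined as positive for malignancy". Patients whose samples show no malignancy or are indeterminate start as negative. "In such cases, the attending physician will conduct follow-up for at least 12 months", and the final diagnosis is fixed at 12 months. The section lists what makes a false negative and what makes a true negative. It has no class for a negative patient who is lost before any of those events.

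Table 2 (Objectives and endpoints) defines sensitivity as "Malignancy confirmed by modality)/(Number of malignancies confirmed at 12-month follow-up". It defines yield (labelled diagnostic accuracy) as malignant plus benign diagnoses over all biopsied lesions. The Abstract names yield and sensitivity among the primary outcomes.

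The sample size section calculates for "equality of paired proportions with a two-sided significance level of 0.05 and 80% power" and then adds an allowance "With an estimated dropout rate of 5% due to the loss of patients during follow-up", reaching 142.

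**The concern.** A flat 5% allowance is harmless when loss is unrelated to the result. Here it cannot be, because a patient positive on any index sample already has a final diagnosis and cannot lose it. The patients left unresolved are negative on needle, forceps and BAL alike. If one of them has cancer, both tools missed it, and Table 2 never counts that miss. The numerator of sensitivity is complete on the day of the procedure, while its denominator depends on follow-up.

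The stake is the absolute figure. The Discussion sets ENB against published yields of 67–84%, so readers will compare the trial's percentages with others. An error of a few points, always in the favourable direction, matters in that setting.

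The sample size section also sits awkwardly with Table 2. It deducts lost patients from a calculation for yield, whereas Table 2 keeps every biopsied lesion in the yield denominator.

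**Working it through.** **1. The plan's own figure.** Inputs from the sample size section: two-sided 0.05, 80% power, difference 0.15, discordance 0.39.

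n = [1.96·√0.39 + 0.8416·√(0.39 − 0.15²)]² / 0.15² = 133.7, so 134. Then 134/0.95 = 141.05, so 142. The stated figure reproduces. The planned loss is 0.05 × 142 = 7.1, about 7 patients, and the division by 0.95 treats them as not evaluable.

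**2. Sensitivity after loss.** Let M be the true number of malignancies, S the true sensitivity, L = 7 the index-negatives lost, and m the share of those lost who have cancer. Lost cancers were missed by both tools, so the numerator S·M does not change:

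reported sensitivity = S·M / (M − m·L)

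This can never be below S. It equals S only when m = 0.

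The article gives no prevalence and no assumed sensitivity. I take prevalence from 60% to 90% and use the plan's 67% and 82% as illustrative sensitivities.

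| Prevalence | M | S·M single / combined | All 7 malignant (m = 1) | Half malignant (m = 0.5) |
|---|---|---|---|---|
| 60% | 85.2 | 57.1 / 69.9 | ÷78.2: 73.0% / 89.3% | ÷81.7: 69.9% / 85.5% |
| 75% | 106.5 | 71.4 / 87.3 | ÷99.5: 71.7% / 87.8% | ÷103.0: 69.3% / 84.8% |
| 90% | 127.8 | 85.6 / 104.8 | ÷120.8: 70.9% / 86.8% | ÷124.3: 68.9% / 84.3% |

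The worst case is feasible. The combination misses 0.18·M = 15.3 to 23.0 cancers, which is more than 7 (ignoring any that BAL alone finds).

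**3. A mild case.** Suppose the 7 losses fall at random over all 142 patients. Lost index-positives keep their diagnosis, and lost missed cancers number 0.18·M × 7/142. Reported sensitivity is S / (1 − 0.18 × 7/142) = S / 0.9911. That gives 67.6% and 82.7%, a shift of less than one point.

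**4. Yield, if the 7 were removed.** Let b be the share of lost patients whose result counts as a success under Table 2. Yield = (Y·142 − b·7)/135.

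- b = 0: 95.14/135 = 70.5% and 116.44/135 = 86.3%.
- b = 1: 88.14/135 = 65.3% and 109.44/135 = 81.1%.

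Yield rises only while b is below 67% (single) or 82% (combined), and falls above that. If all 142 stay in, as Table 2 is worded, nothing is removed.

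**5. The paired test.** McNemar's statistic uses discordant pairs only. On the plan's assumptions these are about 0.33 × 0.82 × 142 = 38 and 0.67 × 0.18 × 142 = 17, so (38 − 17)²/55 = 8.02. Removing patients with the same result on both sides leaves it at 8.02.

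**The case against.** The strongest reply is that the article states no rule for excluding lost patients. The 5% only enlarges the sample, Table 2 already divides yield by all biopsied lesions, and handling of missing diagnoses may be set out in a full protocol or analysis plan not shown here. The 5% is also a loss of patients, not of negatives, so fewer than 7 may end up unresolved. The sensitivity bias needs at least one lost cancer, and prevalence is an outside assumption.

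Most of this limits the size of the point. It does not remove it, because the sensitivity formula is printed as the definition of a primary outcome. Applied as written alongside the loss that the plan itself expects, it omits unconfirmed misses. A later document could add bounds, but this definition does not.

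A reader might go further and infer that dropping lost patients removes only failed biopsies, and so inflates yield by about four points for every modality. The documents do not support that. Benign diagnoses count as successes in Table 2 and also belong to the initially negative group, so a lost patient may be a success. Take 120 cancers as an illustration, with 98 found by the combination and 116 combined successes in all. There are then 142 − 98 = 44 index-negatives, of whom 116 − 98 = 18 are benign successes. Losing 7 of the 44 at random gives (116 − 7 × 18/44)/135 = 83.8% against 116/142 = 81.7%, about two points. Even that requires a removal which Table 2 does not call for.

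**Conclusion.** The point holds for sensitivity. Missing final diagnoses are confined to index-negatives, and the Table 2 denominator turns that into a bias that can only be upward, for each tool and for the combination. With 7 index-negatives lost, all of them malignant, 67% reads as about 71–73% and 82% as about 87–89%. With half malignant the readings are about 69–70% and 84–86%. With loss spread evenly over all patients the shift is under one point. These figures rest on an assumed prevalence of 60–90% and on using the plan's yields as sensitivities.

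No fixed direction can be claimed for yield. The McNemar comparison is unaffected by losses that are concordant, so what is at risk is the absolute estimates, not the powered test. The sample size of 142 is not in error on this account, but its section and Table 2 should agree on who is analysed.

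**What to change.** For sensitivity, specificity and NPV, report the complete-case figure with two bounds: all unresolved index-negatives set to malignant, then all set to benign. For sensitivity the benign bound equals the complete-case figure, and the malignant bound adds the unresolved lesions to the denominator. At 75% prevalence with all 7 lost being cancers, the complete-case 87.8% would carry a lower bound of 87.33/(99.5 + 7) = 82.0%, which is the true value in that scenario.

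In the sample size section, state that patients lost to follow-up stay in the Table 2 denominator of all biopsied lesions for yield. Apply the same two bounds to any whose benign status is unresolved. Scoring every unresolved negative as non-diagnostic is not needed, and would depart from the Table 2 numerator wherever a modality gave a benign diagnosis.

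The cost is a few extra table rows, a sentence in the sample size section, and slightly less favourable reported figures.

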## Methods/design

### Study design and subject eligibility

We designed a prospective, randomized trial to evaluate the synergistic diagnostic yield of ENB-guided needle aspiration biopsy and ENB-guided forceps biopsy by performing biopsy with both the devices in a random order (Fig. 1). This study aims to enroll approximately 142 participants from a tertiary center in South Korea by 11 pulmonary physicians. All consecutive patients over the age of 18 years who are candidates for an elective ENB procedure for histopathological evaluation of peripheral lung lesions suspected of malignancy but predicted to be unreachable with conventional bronchoscopy alone are eligible for enrollment. The exclusion criteria are: (1) patients unable or unwilling to provide informed consent or comply with the follow-up schedule; (2) patients who have participated in an investigational drug or device research study within 90 days of enrollment, with possible interference with this study; (3) patients with a history of intolerance to moderate sedation or allergies to any of the sedatives planned to use, those with comorbidities contraindicating the bronchoscopy procedure, those on mechanical ventilation or who underwent a tracheostomy, or those who are pregnant; (4) patients with multiple lesions that need to be sampled with ENB-guidance; and (5) patients who were initially planned to undergo ENB but successfully underwent biopsy from a visible endobronchial tumor lesion, which precluded the need for electromagnetic navigation, or those who failed to perform ENB-guided biopsy with both modalities.

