### Randomization and baseline evaluation

After providing informed consent, the participants will be randomly allocated to a study group (needle precedence group or forceps precedence group). They will initially undergo ENB-guided biopsy with the modality of the allocated group (needle or forceps) followed by a biopsy with the other modality. Randomization will be performed by an independent statistician using a computer-generated list using SAS version 9.4 (SAS Institute, Cary, NC, USA). The attending physicians have no role in the assignment process and will be blinded to the allocation. The physicians who will perform the ENB procedure are also blinded to the allocation until the preparation of ENB on the day of the procedure.

The enrolled participants will be evaluated for demographic, clinical, and radiological characteristics at baseline (within 30 days of the procedure) and on the procedure day. The complete list of baseline demographic data and lesion characteristics evaluated with the pre-procedural chest CT is listed in Table 1. Additionally, the pre-procedural probability of malignancy of the lesion will be evaluated for each lesion using the Brock model [3].

**Table 1 Tab1:** Basic characteristics of the participants

Demographics
Age (years)
Sex
Race
Smoking status
Pack-years smoked
Family history of lung cancer
Clinical characteristics
Performance status
History of lung cancer diagnosis
History of malignancies other than lung cancer
Prior invasive lung procedures and surgery
Radiological characteristics
Lesion location (lung lobe)
Lesion type (solidity)
Lesion size
Size of solid proportion
Lesion shape (speculated margin, cavity formation, bubble lucency)
Pre-procedural probability of malignancy
Distance from lesion to pleura
Emphysema surrounding lesion
Interstitial fibrosis surrounding lesion
Bronchiectasis surrounding lesion
Presence and type of bronchus sign
Combined lymphadenopathy
Positivity on positron emission tomography (if applicable)
Procedural characteristics
Preceded modality
Capability to navigate and localize the lesion
Number of biopsy attempts (for each modality)
Acquisition of a core tissue available for histologic examination (for each modality)
Procedure duration
Sequential linear EBUS for nodal staging
Total dose of sedatives used

*EBUS* Endobronchial ultrasound

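### Each tool's yield is pooled over first and second position, so any position effect shifts the stated gain from combining by half its size; the gain over the first-used tool should be prespecified by randomised sequence

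*Protocol article*

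**What the plan says.** Under Study design and subject eligibility, the article describes evaluating the synergistic yield "by performing biopsy with both the devices in a random order". Under Randomization and baseline evaluation, the two arms are a needle-first and a forceps-first group, and the allocated tool is "followed by a biopsy with the other modality". Under Procedures, each tool is to be tried at least three times, with no upper limit.

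Table 2 (Objectives and endpoints) states: "Primary endpoints will be calculated separately for needle aspiration, forceps biopsy, and the combination of the two". Position is not mentioned there. The sample size section sets the target at a 15-point difference between individual modalities and their combination (67% against 82%). It gives the counts as "71 in each group, and 142 biopsies for each modality and combination", and then says: "To compare the paired proportions, McNemar’s test will be used". The order of the tools appears among the recorded variables only as a procedural characteristic in Table 1, "Preceded modality".

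**The concern.** The only thing this trial randomises is which tool goes first, and no stated analysis uses it. In every patient one of the two results is obtained after the other tool has been used on the same lesion. Pooling a tool's 142 results thus averages 71 first-position results, which resemble using that tool alone, with 71 second-position results, which may not.

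This matters most for the contrast that sized the trial. The Discussion names the cost of an additional tool as a reason against a multi-tool strategy without clear benefit. That makes the practical question what a second tool adds once the first has been used. The direct comparator is the first-used tool, not a tool averaged over both positions. If yield depends on position in either direction, the pooled gain answers a somewhat different question, and the stated analysis would not show the reader that it does.

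**Working it through.** **The plan's own figure.** Inputs from the sample size section: d = 0.15, discordance pd = 0.39, two-sided alpha 0.05, power 80%, dropout 5%.

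n = [1.960·√0.39 + 0.842·√(0.39 − 0.15²)]² / 0.15² = 133.7, rounded up to 134. Then 134/0.95 = 141.05, rounded up to 142. The stated total reproduces, and nothing below changes it.

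**Share of second-position results.** With 71:71 allocation, each tool has 71 first-position and 71 second-position results: 71/142 = 50%.

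**Effect of pooling.** Let delta be first-position minus second-position yield, averaged over the two tools, with equal groups. Then:

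- pooled single-tool yield = first-position yield − delta/2
- combination − pooled single = (combination − first-used tool) + delta/2

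For one tool taken separately, the same identity holds if the combined yield does not depend on the order.

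The documents give no value for delta, so a range is assumed. Take the pooled single-tool yield as 67% and the combination as 82%, so that the pooled analysis shows a 15-point gain:

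| Assumed delta (points) | First position | Second position | Gain over first-used tool | Pooled minus first-used gain |
|---|---|---|---|---|
| −10 | 62.0% | 72.0% | 20.0 | −5.0 |
| −5 | 64.5% | 69.5% | 17.5 | −2.5 |
| 0 | 67.0% | 67.0% | 15.0 | 0 |
| +5 | 69.5% | 64.5% | 12.5 | +2.5 |
| +10 | 72.0% | 62.0% | 10.0 | +5.0 |

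**Extreme case.** Suppose the second tool adds nothing, so that the combination equals the first-used tool, but second-position yield is lower by delta. A single pooled tool then falls short of the combination in a proportion delta/2 of patients. Count the combination as diagnostic when either tool is. All discordant pairs then run one way, and an exact McNemar test needs at least 6 of them (2·0.5⁶ = 0.031; five give 0.063). With n = 135 (142 × 0.95 = 134.9), P(Bin(135, delta/2) ≥ 6) is about 67% for delta = 10 points, 12% for 5 points and 0.3% for 2 points.

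**Needle versus forceps.** With a position effect common to both tools and a and b patients in the two sequences, the bias is delta·(a − b)/(a + b). At 71:71 it is zero. At 71:64 with delta = 10 points it is 10 × 7/135 = 0.5 points.

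**What the alternative can support.** Combination versus first-used tool is a within-patient contrast.

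| True gain | Exact power, n = 135 (both sequences) | Exact power, n = 67 (one sequence) |
|---|---|---|
| 15 points | over 99.9% | about 95% |
| 10 points | 99% | 67% |

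For precision, 20/135 gives a 95% Clopper-Pearson interval of 9.3% to 21.9%, and 10/67 gives 7.4% to 25.7%.

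**The case against.** The strongest reply is that this rests on silence in a condensed article. The 142 per modality is a sample-size count and does not forbid an analysis by sequence. Naming McNemar's test excludes nothing, the order is recorded, and a statistical analysis plan that is not shown may contain period terms and sensitivity analyses. This is fair as far as it goes. If such an analysis exists, the sponsor need only confirm it. But the article states its denominators and its paired test in a section on the primary statistical plan. The point is that this stated choice gives a weaker comparator than the design allows, and not that detail is missing.

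Four stronger readings are tempting, and the documents support none of them:

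- *The gain is misestimated.* That follows only if yield depends on position. The documents give neither sign nor size, and a better second position would make the pooled gain conservative.
- *A position effect could not be detected.* It can be estimated, because order is randomised and recorded.
- *Needle versus forceps is biased.* Balanced order protects that contrast; the arithmetic gives about half a point in an unfavourable case.
- *The sample size is wrong for this reason.* The figure of 142 reproduces and does not depend on this point.

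It is also fair that the overall gain over the first-used tool averages two different starting tools, and so targets something other than the per-tool endpoints in Table 2. For that reason it should stand beside the pooled yields, with the sequence-specific gains shown, and should not replace them.

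**Conclusion.** The point holds in a conditional form. The stated plan pools each tool over both positions and states no analysis by the randomised order. The pooled gain therefore equals the gain over the first-used tool plus delta/2. The shift is 2.5 or 5 points for an assumed position effect of 5 or 10 points, in either direction, against a design difference of 15 points. It is zero without a position effect. The extreme case shows that a large drop in second position could pass for a benefit of combining, but it assumes that the second tool adds nothing, and it fades quickly as the drop shrinks.

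The result rests on near-equal sequence groups and on counting the combination as diagnostic when either tool is. The needle-versus-forceps conclusion also assumes a position effect common to both tools. The analysis should be amended because a more direct comparator is available from data already being collected.

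**What to change.** Before results by sequence are examined, prespecify:

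1. The within-patient gain of the combination over the first-used tool, with a confidence interval, by randomised sequence (forceps added to needle, needle added to forceps) and overall, alongside the pooled per-tool yields.
2. A check for a position effect: the Mainland-Gart test, or a paired model with tool and position. Do not add a tool-by-position term. With two tools in two orders it is the sequence itself and is constant within a patient, so a conditional logistic model cannot estimate it.
3. The first-position-only comparison of needle and forceps as a sensitivity analysis. It is free of carry-over but is a between-group comparison, with roughly 51% to 54% power for 67% against 82% at 67 to 71 per group. It cannot carry the main conclusion.

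This changes analysis wording only. The order is already recorded under "Preceded modality", and no additional patients are needed. The downside is lower precision for the sequence-specific gains, which rest on about 67 to 71 patients each.
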